## Abstract

**Background:**

Despite a variety of efficient and cost-effective antihypertensive medication, hypertension remains a serious health and economic burden. High consumption of cardiovascular drugs in the Slovak Republic does result neither in better hypertension control nor in significant decrease in cardiovascular mortality. At the same time, Slovakia has alarmingly low patients’ adherence to medication intake. Studies have shown the efficiency of short messaging service (SMS) reminders to improve patients’ adherence and health outcomes at low costs. Since SMS is popular among Slovaks, this approach may be feasible also in Slovakia. The primary objective is to assess if daily SMS reminders of antihypertensive medication intake provided by pharmacists in addition to the standard pharmaceutical care increase the proportion of adherent older hypertensive ambulatory patients.

**Methods:**

The SPPA trial is a pragmatic randomized parallel group (1:1) trial in 300 older hypertensive patients carried out in community pharmacies in Slovakia. Trial pharmacies will be selected from all main regions of Slovakia. Trial intervention comprises daily personalized SMS reminders of medication intake embedded into usual pharmaceutical practice. The primary outcome is a combined adherence endpoint consisting of subjective self-reported medication adherence via the eight-item Morisky Medication Adherence Scale (MMAS-8) and objective pill count rate. Secondary outcomes include: change in the MMAS-8; comparison of adherence rates using pill count; change in systolic blood pressure; and patient satisfaction. Also, direct treatment costs will be evaluated and a cost-effectiveness analysis will be carried out.

**Discussion:**

The SPPA trial engages community pharmacists and mobile health (mHealth) technologies via evidence-based pharmaceutical care to efficiently and cost-effectively addresses current main healthcare challenges: high prevalence of hypertension; overconsumption of cardiovascular medicines; low adherence to medication treatment; and resulting uncontrolled blood pressure. The results may identify new possibilities and capacities in healthcare with low additional costs and high value to patients.

**Trial registration:**

ClinicalTrials.gov, NCT03105687. Registered on 07 March 2017.

**Electronic supplementary material:**

The online version of this article (doi:10.1186/s13063-017-2063-8) contains supplementary material, which is available to authorized users.

## Background

Cardiovascular diseases caused 17.7 million deaths worldwide [1], including 25,906 in Slovakia [2] in 2015, accounting for 31.3% and 48.13% of the overall mortality rate in the world and Slovakia, respectively. One of the main cardiovascular risk factors is hypertension [3]. Its prevalence reaches 30–45% among European countries [3, 4] as well as in Slovakia [5–7], increasing with age [8]. Health consequences of hypertension in older patients are more complex and severe [9]. Additionally, hypertension also represents a significant economic burden [10, 11]. In 2014, Slovakia had the third highest cardiovascular drugs utilization among OECD countries (683.4 DID; 37.6% of total drug consumption) [12]. A total of €155.9 million were spent on cardiovascular drugs [12], while complications resulting from insufficiently treated hypertension are even more expensive [13]. High consumption of cardiovascular drugs in Slovakia poses a significant economic burden both to the healthcare system and to the patients [14].

Despite a wide range of both efficient and cost-effective antihypertensive medicines, blood pressure control remains insufficient. Recent findings of the EURIKA study report only 50% blood pressure control among European countries [15]. National studies estimate that only 21–31% of Slovak patients have controlled hypertension [16, 17]. Poor adherence to antihypertensive medication intake belongs to the key risk factors of uncontrolled blood pressure [18, 19] resulting in increased risk of stroke, hospitalization, and premature death [20–22]. World Health Organization (WHO) estimates the overall adherence to medication intake in patients with chronic diseases at 50% [23, 24], while the latest European results show a varying adherence in the range of 26–70% [25]. Seriousness of this problem in Slovakia best demonstrate the results of local studies reporting 15–19% adherence rates (ARs) among Slovak patients [26–30]. Adherence to medication is a complex behavior influenced by multiple factors associated with the patient, healthcare providers, healthcare system, and specific treatment. These may result in intentional or unintentional patients’ non-adherence. While intentional non-adherence is a result of patients’ active decision not to take their medication as prescribed, unintentional non-adherence is caused by other factors such as forgetfulness, misunderstanding of the medication regimens, access to medication, or language barriers [31]. Several interventions to increase patients’ adherence to medication intake have been developed [32]. However, the majority of them are associated with high costs, time, and health professional resources, providing promising but uncertain and variable results [33]. Since the Slovak healthcare system lacks financial as well as professional human resources [34, 35], most of the adherence-increasing interventions are not feasible in Slovakia.

Technological progress has recently resulted in the implementation of various mobile technologies in healthcare to improve patients’ clinical outcomes as well as the effectiveness of healthcare system [36, 37]. Studies have confirmed the effectiveness of short message service (SMS) reminders on improving adherence to medication intake, health status, and attendance at medical appointments of patients with infectious diseases [38–48]. Latest systematic reviews suggest that SMS reminders may also be effective in the management of chronic diseases [49, 50]. In 2015, Global System for Mobile communication network covered 92.0% of the Slovak territory and 100.0% of the Slovak population [51]. Additionally, national telecommunication statistics report 491.6 SMS sent per one inhabitant in 2015, demonstrating that SMS are a popular means of communication among Slovaks [52]. Considering all previously mentioned facts, we hypothesize that SMS reminders present a suitable approach to improve patients’ adherence to medication intake in Slovakia.

Pharmacists play a vital role in the healthcare system and can substantially improve the value of pharmacotherapy [53–55]. Studies have shown that pharmacists’ interventions in chronic cardiovascular disease management significantly improve patients’ outcomes [56–58]. Furthermore, local studies have proven that high-quality pharmaceutical care improves both the adherence to medication intake and blood pressure control in hypertensive patients [26, 59, 60].

The need of a multidisciplinary approach towards poor adherence to medication intake is being widely stressed and encouraged [23, 61, 62]. At the same time, the WHO concludes that improving patients’ adherence may have a greater effect on the health than any other improvement in therapy [23]. Therefore, the presented pragmatic trial explores the possibilities of mobile health (mHealth) interventions provided by pharmacists in improving patients’ adherence to antihypertensive medication intake in Slovakia. We hypothesize that personalized daily SMS reminders of antihypertensive medication intake provided by pharmacists in addition to standard pharmaceutical care (sPhC) will increase the proportion of adherent older ambulatory patients with hypertension from 30% to 49%.

## Methods

### Trial objectives

The primary objective of the SPPA trial is to assess if daily SMS reminders of antihypertensive medication intake provided by pharmacists in addition to the sPhC increase the proportion of adherent older hypertensive ambulatory patients.

Secondary objectives include: (1) comparing the change of self-reported adherence using the eight-item Morisky Medication Adherence Scale (MMAS-8); (2) comparing ARs measured via pill count between trial groups; (3) comparing the change in systolic blood pressure; (4) investigating the effect of SMS reminders on improving patients’ adherence and systolic blood pressure control (treatment effects) across subgroups; and (5) collecting and reporting patients’ satisfaction with daily SMS reminders.

We will report up-to-date ARs of older hypertensive patients in Slovakia and assess the impact of sociodemographic characteristics on patients’ adherence to antihypertensive medicines. Furthermore, we will evaluate the MMAS-8 questionnaire in our trial population. Additionally, we will carry out a simple cost-effectiveness analysis from the payers’ perspective.

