### Trial design

The SPPA trial is designed as a multicenter assessor-blinded, controlled, randomized, superiority, pragmatic trial to assess the effectiveness of daily SMS reminders of antihypertensive medication provided by pharmacists in addition to sPhC compared with sPhC only. Patients will be individually randomized into two parallel groups in a 1:1 allocation ratio. Participants in the intervention group will receive daily SMS reminders of medication intake, whereas participants in the control group will receive sPhC only. The trial will last three months with a recruitment period of two months. The Standard Protocol Items: Recommendations for Interventional Trials (SPIRIT) checklist for study protocols [63] is provided in Additional file 1. Details about the pragmatic design of the SPPA trial are provided in the PRagmatic Explanatory Continuum Indicator Summary (PRECIS-2) table of scores for trial domains and the PRECIS-2 wheel scheme [64] in Additional file 2.

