### Inclusion criteria

Age ≥ 55 years (from the day of the 55th birthday inclusive);Diagnosis of primary hypertension (I10 according to ICD-10 [65]);Filling of antihypertensive prescription(s) at trial recruitment (Visit 1);Duration of antihypertensive drug treatment for at least one year without any discontinuation;Ownership of a mobile phone for personal use with the ability to open and read SMS;Understanding of Slovak language on native-speaker level;Informed consent for participation in the clinical trial and personally signed informed consent form.

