### Exclusion criteria

Exclusion criteria assessed prior to patient enrolment:Planned hospitalization during the trial period;Biological impairment affecting the ability to read the SMS (e.g. loss of vision, visual field cuts, aphasia);Living in the same household with another trial participant;Participation in another clinical trial.

Exclusion criteria assessed after patient enrolment:Hospitalization during the trial period;Patient informs he/she will not be able to participate in the trial;Withdrawal of informed consent.

We have strived to maintain broad eligibility criteria to ensure our trial population best reflects the real-world population of patients for whom the intervention is intended. Nevertheless, we accepted some inclusion and exclusion criteria, which can strengthen the validity of the trial’s results while not introducing selection bias. We focus on patients with primary hypertension to limit the confounding influence of secondary hypertension causes both on patients’ adherence to medication and resulting blood pressure control. Patients with other co-morbidities are eligible to participate in the study. We will recruit patients while filing their prescription at the trial pharmacy. According to Slovak health legislation, physicians are allowed to prescribe medication to chronic patients for a maximum of three months. Hence, patients who are collecting their medicines at the day of the recruitment will in most cases begin to take the pills out of the collected medication package on the next day (first day of the intervention), enabling the precise calculation of pill count rates. Furthermore, chronic patients in Slovakia visit the pharmacy usually in three-month cycles. We will include only patients who take their antihypertensive medication for at least one year because these patients are considered to have reached their acceptance phase of medicinal treatment and consequently are at lower risk of early therapy discontinuation due to non-acceptance [66]. Trial participants hospitalized during the trial will be excluded since during their hospital stay healthcare providers will manage their medication resulting in the redundancy of SMS reminders.

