### Data collection, handling, and monitoring

Trial data will be collected at Visit 1 (day of patient enrolment) and at Visit 2 (follow-up visit after three months). Table 2 provides and overview of all case report forms that will be used in the trial for data collection. Furthermore, we will actively seek and collect signals of adverse events associated with antihypertensive medication intake reported by the participants. We will also collect anonymous reasons for participation refusal and discontinuation of participation. All trial forms and materials constituting the Appendixes of the SPPA trial protocol are available in Additional file 3.

**Table 2 Tab2:** Overview of Case Report Forms in the SPPA trial

Case Report Form/Questionnaire	Details	Time Point
Case Report Form Visit 1 – PART A	Antihypertensive medication specification Mobile phone number for SMS reminders Preferred time of SMS reminder	Visit 1
Case Report Form Visit 1 – PART B	Blood pressure measurement	Visit 1
Case Report Form Visit 1 – PART C	Medication adherence measurement via MMAS-8	Visit 1
Case Report Form Visit 1 – PART D	Patient information (Sociodemographic and health information, information on mobile phone usage)	Visit 1
Case Report Form Visit 2 – PART A	Medication adherence measurement via pill count	Visit 2
Case Report Form Visit 2 – PART B	Blood pressure measurement	Visit 2
Case Report Form Visit 2 – PART C	Medication adherence measurement via MMAS-8	Visit 2

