#### Mean adherence rates after three months calculated via pill count

The mean difference in adherence reported as AR (%) measured at Visit 2 between the intervention and the control groups will be calculated. The effect size and the corresponding 95% CI will be reported. We will use a two-tailed t-test to compare the difference between these independent means as well as their robust versions that are recommended when conditions for these tests are violated while preserving high statistical power.

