#### Other outcomes analyses

We will assess internal consistency of the MMAS-8 scale in our trial population by Cronbach’s alpha coefficient and reliability of the summed score by McDonald’s hierarchical omega, which has been shown to be a superior measure to Cronbach’s alpha [97]. We will also provide the measures of sensitivity and specificity of MMAS-8 related to correct prediction of high blood pressure. Of interest is also the relationship between two measures of adherence (MMAS-8 and pill count), which will be analyzed using correlation coefficients (Pearson and Kendall tau). Additionally, regression techniques to analyze the impact of co-variables, such as: age, gender, education level, social status, place of residence, number of daily doses, co-medication, co-morbidities (concomitant diseases, smoking status), and pharmacy on patients’ adherence will be applied.

Since we are interested in providing relevant information for the decision-making process, we will conduct a simple cost-effectiveness analysis. Here, we will focus only on the differential costs that depend on the choice of alternative care (usual pharmaceutical care or SMS reminder).

Finally, we will collect, report, and perform a qualitative analysis of the refusal to participation in the trial and withdrawal from the trial rates.

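### The adherence rate promised for older hypertensive patients in Slovakia will describe persistently treated, refilling, phone-owning patients, and the Visit 2 part of it is reminder-free only in the control arm

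*Protocol article*

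**What the plan says.** Under Trial objectives, after the primary objective and the five numbered secondary ones, the protocol adds: "We will report up-to-date ARs of older hypertensive patients in Slovakia and assess the impact of sociodemographic characteristics" on adherence. The Discussion repeats that the trial will supply current adherence data for this national population. Trial setting says the choice of pharmacies will make the results widely generalisable to older hypertensive Slovaks. The rationale under Exclusion criteria says the chosen criteria bring in no selection bias.

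The Inclusion criteria require: "Duration of antihypertensive drug treatment for at least one year without any discontinuation". They also require that the patient is filling an antihypertensive prescription at Visit 1 and owns a mobile phone.

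On measurement, Table 2 lists "Medication adherence measurement via pill count" for Visit 2 only, while MMAS-8 is taken at both visits. The planned pill-count analysis is by arm: "The mean difference in adherence reported as AR (%) measured at Visit 2 between the intervention and the control groups will be calculated". For determinants of adherence, Other outcomes analyses plans "regression techniques to analyze the impact of co-variables", followed by an illustrative list that does not name trial arm. No section says which visit, arm or measure will supply the descriptive rate.

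**The concern.** Two things separate the promised figure from what the design can deliver.

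The first is the population. A year of uninterrupted treatment is itself a form of adherence. The protocol justifies the one-year rule by saying that such patients are less likely to stop early. That describes a selection effect, yet the same section says the criteria introduce no selection bias. For the randomised comparison the statement is harmless, because both arms pass through the same filter. For a descriptive rate presented as national, the filter acts directly on the result.

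The second is timing. The pill-count rate and the combined endpoint are first observed when half the patients have had daily reminders for three months. If the source of the descriptive rate is left open, a reader cannot tell whether a published figure reflects usual care or a mixture of treated and untreated patients.

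At stake is one descriptive conclusion: what the trial may say about how adherent older hypertensive patients in Slovakia are.

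**Working it through.** **1. The plan's own figure.** The protocol gives no sample size or precision for the descriptive rate. Its primary calculation (Sample size calculation: w = 0.2, alpha 0.05, power 0.9) reproduces: the noncentral chi-square with 1 df gives 263 against 264 stated, and power at 264 is 0.901. With 10% attrition, 264/0.9 = 293.3, so 300 is enough. The denominators used below are 300 randomised, 150 per arm, and 150 × 0.9 = 135 per arm after attrition.

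**2. Stated population against sampled population.**

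| Stated target | Admitted patients |
|---|---|
| Older hypertensive patients in Slovakia (Trial objectives, Discussion) | Age 55 or over with primary hypertension |
| No restriction on treatment history | At least one year of treatment, uninterrupted |
| No restriction on refilling | Filling a prescription at Visit 1 in a trial pharmacy |
| No restriction on phone ownership | Owns a mobile phone and can read SMS |

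**3. Direction of the error.** Let e be the share of the wider population that the rules exclude, p the adherence rate among those admissible and q the rate among those excluded.

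- Wider rate = (1 − e)p + eq
- Overstatement = p − [(1 − e)p + eq] = e(p − q)

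This is positive whenever q < p. That is to be expected for patients excluded because they interrupted treatment or do not refill. For phone ownership the sign is not obvious. The documents give neither e nor q, so no size follows. At p = 30% the overstatement cannot exceed 30e points (the case q = 0).

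**4. What is measured before or without reminders** (Tables 1 to 4).

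| Measure | Visit 1 | Visit 2, control | Visit 2, intervention |
|---|---|---|---|
| MMAS-8 | all patients, before any reminder | no daily reminders | after 3 months of reminders |
| Pill-count rate | not taken | no daily reminders | after 3 months of reminders |
| Combined endpoint | cannot be formed | no daily reminders | after 3 months of reminders |

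Reminders start the day after enrolment, so Visit 1 MMAS-8 is untouched by them.

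**5. What pooling at Visit 2 would do.** With 1:1 allocation and the protocol's 30% and 49%: (30 + 49)/2 = 39.5%, which is 39.5 − 30 = 9.5 points above the control rate.

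**6. Precision without pooling.** Half-width = 1.96 × √[p(1 − p)/n], at p = 0.30:

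- Control arm, n = 150: 1.96 × √(0.21/150) = 0.073, or ±7.3 points
- Control arm, n = 135: 1.96 × √(0.21/135) = 0.077, or ±7.7 points
- Baseline MMAS-8, n = 300, with 30% assumed for that measure too: 1.96 × √(0.21/300) = 0.052, or ±5.2 points

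These apply to proportions. The protocol gives no SD for the mean pill-count rate, so its interval cannot be calculated in advance.

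**The case against.** The best defence is that usable data are already planned. Baseline MMAS-8 is collected in everyone, and Subgroup analysis itself calls it a self-reported adherence rate. The pill-count rate is analysed by arm, so a control-arm value will exist. The entry rules are stated openly, and the trial is aimed at forgetfulness in patients on continuing treatment, who remain eligible. The aim is one descriptive sentence in a condensed article, and the choice of arm and visit for a descriptive table may be set out in a fuller document. Most of this stands. It keeps the point minor, but it does not reconcile the national wording and the no-selection-bias claim with the entry rules.

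Four stronger readings might be inferred. The documents do not support them.

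- *The objective cannot be met.* It can, from baseline MMAS-8 and control-arm data, for a narrower population.
- *The published rate will mix the arms.* No section says so. The 39.5% shows what to avoid and is not a planned result.
- *Recruitment timing makes a fully adherent patient twice as likely to be sampled as a half-adherent one.* The protocol says "The trial will last three months with a recruitment period of two months" and that "chronic patients in Slovakia visit the pharmacy usually in three-month cycles". If patients returned only when their pills ran out, the chance of a refill in 60 days of a 90-day supply would be 60a/90 at adherence a: 67% at a = 1 and 33% at a = 0.5. But the Intervention group section ties the cycle to the three-month prescription limit and the medical visit. On that account a half-adherent patient can return on schedule with pills left over, and the ratio disappears.
- *The rate will look falsely high beside the 15–19% from local studies in the Background.* That depends on how those studies sampled and measured adherence, and they are not shown.

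Nor is leaving trial arm out of the regressions a source of confounding. The covariate list is introduced as examples, and randomised arm is independent in expectation of baseline characteristics. Omitting it costs precision, with some attenuation in a logistic model.

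**Conclusion.** The concern holds in a limited form. The entry rules select for persistence and refilling, so the trial's rate probably overstates adherence among older hypertensive patients in Slovakia. The external-validity and selection-bias statements are too broad for this aim, and the limitations omit it. The direction rests on the assumption that patients excluded for interrupting treatment or not refilling are less adherent than those admitted. The size is unknown.

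For pill count and the combined endpoint, only the control arm gives a reminder-free value. Using both arms would add 9.5 points under the protocol's own assumptions. Even the control arm is not purely usual care: those patients are told the purpose of the trial, receive two SMS messages and are followed up.

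No treatment-effect estimate changes. Severity is minor.

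**What to change.** 1. Restate the descriptive aim as adherence among patients aged 55 or over who are persistently treated, own a mobile phone and refill at trial pharmacies. Make the matching change in the Discussion.
2. Qualify or withdraw, for this aim, the external-validity statement in Trial setting and the selection-bias statement under Exclusion criteria. Add the selection to the limitations.
3. State that the descriptive rate comes from baseline MMAS-8 in all randomised patients, and from Visit 2 pill count and the combined endpoint in the control arm only. Label each measure separately and give 95% confidence intervals.
4. Include trial arm in any covariate regression with a Visit 2 outcome, for precision.

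No new data and no change to eligibility are needed. The cost is a narrower claim and a smaller denominator for the pill-count rate and combined endpoint: 135 to 150 patients instead of 270 to 300 (twice those numbers).
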